### Process evaluation

The process evaluation will focus on several key metrics to assess the effectiveness and efficiency of the AI-enabled systematic screening program. These metrics include the DR detection rate and STDR detection rate, which will measure the program’s ability to identify diabetic retinopathy and sight-threatening diabetic retinopathy, respectively. Visual outcomes, specifically visual impairment (VI) and blindness, will be tracked to evaluate the impact of the program on patient health. The timely referral rate for screening, defined as referrals made within two weeks of contact with eligible PWD for DR screening, and the timely referral rate for management, defined as referrals made within two weeks of contact with eligible PWD diagnosed with STDR, will be measured to ensure prompt follow-up and treatment. Additionally, the treatment uptake rate and follow-up rates will be monitored to gauge patient adherence to recommended care. Lastly, a cost-effectiveness analysis will be conducted, considering both direct and indirect expenses, to determine the financial viability and benefits of the program.

### Program outcomes

The program’s outcomes will be evaluated through metrics such as screening uptake rate, sensitivity, and specificity of AI versus manual system, ROC Curve for AI Diagnostic Accuracy for diagnosis of DR, referral rate, cost-effectiveness, patient and provider satisfaction, follow-up rates, and long-term outcomes. These outcomes will help determine the program’s impact on patient health and healthcare costs. Due to the formatting constraints of the CTRI registry, certain fields were filled in a specific way, which might lead to minor discrepancies between the reported outcomes in the manuscript and the CTRI registry. (Table 1 shows the outcome measurement indicators for the project.).

**Table 1 pone.0324382.t001:** Outcome measurement indicators: SMART DROP project.

Outcome	Definition	Numerator	Denominator
Screening uptake rate	Proportion of eligible patients who underwent DR screening out of the total eligible population.	Number of eligible patients who underwent DR screening	Total number of eligible patients in the population
Sensitivity of AI system	Proportion of true positive DR cases correctly identified by the AI system.	Number of true positive DR cases identified by the AI system	Total number of true DR cases confirmed by manual grading
Specificity of AI system	Proportion of true negative cases correctly identified by the AI system.	Number of true negative DR cases identified by the AI system	Total number of non-DR cases confirmed by manual grading
ROC curve for AI diagnostic accuracy	A graphical plot showing the diagnostic ability of the AI system by plotting true positive rate (sensitivity) against false positive rate (1-specificity).	True positive rate (sensitivity)	False positive rate (1-specificity)
Referral rate	Proportion of screened patients referred for further examination or treatment.	Number of patients referred for further examination or treatment	Total number of patients referred
Cost effectiveness	Ratio of the total costs associated with the screening program to the health outcomes achieved, typically measured as cost per quality-adjusted life year (QALY).	Total costs of the screening program	Total health outcomes achieved (e.g., QALYs gained, cases of blindness prevented)
Patient satisfaction	Proportion of patients reporting satisfaction with the DR screening process and outcomes.	Number of patients reporting satisfaction	Total number of patients who completed the satisfaction survey
Provider satisfaction	Proportion of healthcare providers reporting satisfaction with the AI-assisted DR screening program.	Number of providers reporting satisfaction	Total number of providers who completed the satisfaction survey
Follow-up rate	Proportion of patients who return for follow-up visits after initial DR screening or referral.	Number of patients who return for follow-up visits	Total number of patients advised to return for follow-up visits
Long-term outcomes	Proportion of patients with improved visual outcomes or stable DR over a defined period after screening or treatment.	Number of patients with improved visual outcomes or stable DR over time	Total number of patients tracked for long-term outcomes

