## Introduction

Diabetes Mellitus (DM) is a major public health problem worldwide, affecting over half a billion people (537 million in 2021), with projections indicating an increase to 783 million by 2045. Half of these individuals reside in the USA, China, and India [1]. In 2023, it is estimated that India is home to 101.3 million people with diabetes mellitus (DM) and 136.0 million people with pre-diabetes [2]. Diabetic retinopathy (DR) is a significant microvascular complication of DM, caused by damage to the blood vessels in the retina, leading to vision loss or blindness. The prevalence of DR is increasing due to the rising incidence of diabetes, making it a leading cause of blindness globally and in India [3].

A nationwide multicentric study in India found the prevalence of DM in adults aged 40 years and older to be 18%, DR at 12.3%, and vision-threatening diabetic retinopathy (VTDR) at 4%, estimating 3 million people with VTDR in India [4]. The estimated national prevalence of vision impairment among people with known or undiagnosed diabetes was 21.1% (95% CI (confidence intervals) 15.7–27.7) and blindness was 2.4% (1.7–3.4). A higher prevalence of any vision impairment (30%) and blindness (6.7%) was observed in those with ungradable images (indicating cataract burden). Among known diabetics, vision-threatening diabetic retinopathy and diabetic macular oedema were associated with blindness. Based on the estimated 101 million people with diabetes in 2021, approximately 21 million people in India have vision impairment due to diabetes, of whom 2.4 million are blind, with a higher prevalence observed in those from lower socioeconomic strata [5]. Landmark trials over decades have shown that early detection and treatment of DR can prevent or delay its progression and reduce the risk of vision loss [6–8]. For people with diabetes aged 40 years or above, annual screening followed by eye examinations would cost around 42.3 billion Indian rupees (INR) per year; treating sight problems around 2.87 billion INR per year if 20% of those needing treatment receive it; and lost economic activity around 472 billion INR. Moreover, 2.86 million quality-adjusted life years (QALYs) are lost annually due to blindness and moderate-severe visual impairment (MSVI) [9].

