**Fig 3 pone.0324382.g003:**
[figure not shown]
Study flow chart.

We will invite eligible patients for screening through a call and recall system. Visual acuity in both eyes will be recorded using a tablet with a web-based vision checking application (Peek Vision). Non-mydriatic fundus photography of both eyes will be performed using AI-integrated retinal cameras (Forus, 3 Nethra Classic HD with AI Integration in two facilities, and Remidio, Fundus on Phone with AI integration, in two facilities). These AI tools have undergone internal validation and published by the company prior to its integration into the cameras [30,31]. Our project, we will be conducting a real-world validation to assess the performance and effectiveness of this AI tool in practical clinical settings.

Diabetic retinopathy grading will be conducted as per International Clinical Diabetic Retinopathy severity scale [32]. Sight-threatening diabetic retinopathy (DR) is defined as severe non-proliferative diabetic retinopathy (NPDR), proliferative diabetic retinopathy (PDR), and moderate to severe diabetic macular edema (DME). The referral criteria include any patient with DR, visual acuity less than 20/60, any other retinal pathology requiring referral, or ungradable retinal images, or any combination of these factors.

In the AI-enabled screening process for Diabetic Retinopathy (DR) using fundus images, if no signs of DR are detected by the AI, the patient will receive a label of “no DR diagnosis” at the initial stage. However, if DR is indicated, a trained technician at the Idea Clinic will manually review the images to confirm or rule out DR, and the result will be communicated to the patient by the physician. Simultaneously, all images will undergo further manual grading at the Central Image Reading Center at LVPEI for quality assurance. If this manual grading results in a change in diagnosis, the updated result will be shared with the patient within a week since their initial screening.

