### Sample size

We calculate the sample size to detect meaningful differences in the disease staging of patients between two arms at their first eye consultation. Based on the historic data from LVPEI, we assume a 50% prevalence of STDR among DR patients in the SOC arm. Also, we assume that the prevalence of STDR in the intervention arm at the time of screening in the diabetes clinic would be much lower (approximately 10%). However, patients in early stages of DR may not comply with the referral and hence the prevalence of STDR among patients who complete their first ophthalmology visit may be higher (approximately 25%). Based on these estimates, to achieve a power of 80% with a Type-I error rate of 5%, we estimate a sample size of 60 patients in each arm. Since the additional intervention required for the study is minimal (a short check-up using a camera), we expect that about 80% of the eligible patients will consent to participate. Thus, we will need 75 patients with DR to be identified in the intervention arm. Further, based on the historic data at the IDEA clinics, we estimate that 20% of all new registering diabetic patients will have DR. Thus, we will plan to register and screen 375 new diabetic patients each at IDEA clinics (intervention) and LVPEI clinics (SOC arm).

To evaluate the AI tool’s diagnostic accuracy with sensitivity and specificity set at 80%, a sample size of 246 DR-positive cases is required for sensitivity analysis, and 246 DR-negative cases for specificity analysis, assuming a 95% confidence level and a margin of error of ±5%.Given the estimated 20% prevalence of diabetic retinopathy (DR) in the screened population, a total of 1230 patients will be screened to ensure adequate representation of both DR-positive and DR-negative cases.

To assess patient satisfaction, a sample size of **316 patients** will be selected from both the AI-enabled and routine eye care pathways, calculated to detect a difference in satisfaction rates (80% vs. 65%) with a **95% confidence level** and a **margin of error of ±5%**. Random sampling will be employed to ensure unbiased selection of participants from each pathway. This method will involve assigning unique identifiers to eligible patients and using a randomization tool to select participants, ensuring the sample is representative of the study population.

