### Limitations of the study

• The study is conducted in a private healthcare setup where costs are involved, which may result in the exclusion of some patients who could not afford the screening, potentially leading to missed enrolments.• The use of non-mydriatic fundus photography may limit the quality of imaging due to undilated pupils, potentially affecting the accuracy of DR detection.• The study is not designed as a randomized controlled trial (RCT), which would have required the involvement of multiple health facilities and diabetes clinics to generalize the findings more broadly.

The implementation of the study may face challenges such as variability in AI performance, patient adherence to referrals and follow-up, operational issues across multiple sites, patient acceptance of AI tools, and resource constraints for scale-up. To address these potential challenges, we plan periodic recalibration of the AI system, standardized technician training, and regular quality audits to ensure consistent performance. Technicians will undergo periodic training programs focused on image acquisition techniques, device handling, and identification of common image quality issues. In parallel, we will maintain regular communication with the AI solution providers to incorporate necessary adjustments in the algorithm, particularly to optimize performance based on real-world sensitivity and specificity data. This dual approach is expected to enhance both image quality and the diagnostic accuracy of the AI system over time. Strategies to improve patient adherence will include employing navigators, simplifying referral pathways, and providing education on the importance of timely care. Operational issues will be managed through centralized coordination, cloud-based data management, and regular equipment maintenance. Patient trust in AI tools will be fostered through education, validation of AI outputs by experts, and sharing of success stories. Resource constraints will be mitigated by phased implementation in high-burden areas and leveraging public-private partnerships.

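### The AI sensitivity and specificity in Table 1 cover only patients with gradable images, and the 1230 to be screened makes no allowance for ungradable ones

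*Protocol article*

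**What the plan says.** **Who is screened and referred.** Selection of participants sets no image-quality criterion. Study procedures lists among the reasons for referral "any other retinal pathology requiring referral, or ungradable retinal images". The same section sends all images to two trained graders at the reading centre, and an experienced ophthalmologist makes the final grading of those that are ungradable.

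**How accuracy is measured.** Statistical analysis takes expert grading of the images as the truth. Table 1 gives the sensitivity denominator as "Total number of true DR cases confirmed by manual grading" and uses the matching wording for non-DR under specificity. Table 1 has no row for the ungradable proportion.

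**How the number was set.** Sample size assumes 80% for both measures and asks for 246 patients with DR and another 246 without, so that each measure is estimated to within 5 points at 95% confidence. Expecting one in five screened patients to have DR, it concludes: "a total of 1230 patients will be screened to ensure adequate representation of both DR-positive and DR-negative cases".

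**What is expected of image quality.** Limitations of the study concedes: "The use of non-mydriatic fundus photography may limit the quality of imaging due to undilated pupils". No ungradable rate is given anywhere.

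**The concern.** An image that nobody can grade has no DR status under a reference standard that consists of grading that image. The patient is then neither a confirmed DR case nor a confirmed non-DR case and leaves both rows of Table 1. The programme, however, acts on this result by referring the patient. The accuracy measure thus omits one of the outcomes that the screening pathway produces.

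Study procedures describes the work as a real-world validation of the AI tool, and Limitations of the study says that real-world sensitivity and specificity will inform adjustments to the algorithm. Two camera systems are used, each at two facilities, and Strengths of the study presents the variety of cameras as a way to evaluate accuracy. If the cameras differ in how often they fail to give a gradable image, gradable-only accuracy compares different subsets of patients.

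The planned precision has the same gap. The step from patients screened to DR cases available for sensitivity assumes that every patient gets an image-based status.

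**Working it through.** **Inputs from the Sample size section:** sensitivity and specificity 0.80, 95% confidence, margin 0.05, DR prevalence 0.20 among those screened, 1230 screened. **Assumed, because the article gives no figure:** a patient-level ungradable rate u of 5, 10 or 20%, equal in DR and non-DR.

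**Step 1. Reproduce the plan.** n = 1.96² × 0.80 × 0.20 / 0.05² = 245.9, rounded up to 246. Total = 246 / 0.20 = 1230. Both figures match exactly, so no allowance for ungradable images is built in.

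**Step 2. Gradable cases from 1230 screened.** DR: 1230 × 0.20 × (1 − u) = 246(1 − u). Non-DR: 1230 × 0.80 × (1 − u) = 984(1 − u). Margin: 1.96 × √(0.16 / n).

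| u | Gradable DR | Sensitivity margin | Gradable non-DR | Specificity margin | Screened needed for 246 gradable DR, 1230/(1 − u) |
|---|---|---|---|---|---|
| 0% | 246 | ±5.0 | 984 | ±2.5 | 1230 |
| 5% | 234 | ±5.1 | 935 | ±2.6 | 1295 |
| 10% | 221 | ±5.3 | 886 | ±2.6 | 1367 |
| 20% | 197 | ±5.6 | 787 | ±2.8 | 1538 |

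Sensitivity loses a little precision. Specificity stays well inside ±5 points throughout.

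**Step 3. Effect on the estimate if ungradable counts as a positive screen.** Take 80% for both measures among gradable patients, and suppose first that the DR status of the ungradable patients is known. Sensitivity over all screened = 0.8(1 − u) + u; specificity = 0.8(1 − u).

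| u | Sensitivity | Specificity |
|---|---|---|
| 5% | 81% | 76% |
| 10% | 82% | 72% |
| 20% | 84% | 64% |

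If ungradable were instead counted as a miss, sensitivity would be 0.8(1 − u) = 76, 72 and 64%. The rule chosen matters more than the margin: at u = 10% the two rules put sensitivity 10 points apart.

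**Step 4. Bounds when the DR status of the ungradable patients is unknown.** Ungradable counts as positive throughout. At u = 10%, 123 of 1230 patients are ungradable.
- All taken as DR: sensitivity = (0.8 × 221.4 + 123) / (221.4 + 123) = 300.1 / 344.4 = 87%; specificity stays at 80%.
- All taken as non-DR: specificity = 0.8 × 885.6 / (885.6 + 123) = 708.5 / 1008.6 = 70%; sensitivity stays at 80%.

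The bounds at this rate are 80 to 87% for sensitivity and 70 to 80% for specificity.

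**The case against.** **The exclusion is inferred.** No sentence says that ungradable images are dropped, and an article may leave indeterminate results to a fuller document. This would carry weight if the article were silent, but it fixes both the reference standard and the denominators, and together they leave these patients out. The missing-data sentences under Ethics do not name ungradable images.

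**Some images will be resolved.** This stands. Images that the AI cannot grade but the readers can remain in the denominators. The gap there is different: no rule says how the AI result is scored. Only images still ungradable after the ophthalmologist's review drop out.

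**Eyes and patients differ.** This also stands. Both eyes are photographed, so a patient with one gradable eye may still receive a status. The rates assumed above must be read at patient level and could be lower than a rate per eye.

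**The all-screened measure is a different quantity.** Table 1 concerns diagnosis of DR, whereas the referral rule also covers visual acuity and other pathology. That is a reason to report the all-screened result beside the gradable-only one, not in its place.

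**Readings that go too far.** A reader might infer that ±5 points also fails for specificity; the expected 984 non-DR patients rule that out. A reader might also take the Introduction's "A higher prevalence of any vision impairment (30%) and blindness (6.7%) was observed in those with ungradable images" as showing that the excluded patients carry more DR. Those figures concern vision loss, the article links them to cataract burden, and the natural comparators there (21.1% and 2.4%) are overall national estimates, not a gradable group. Finally, a reader might say that the plan conceals referrals caused by image failure. Referral rate is a separate outcome in Table 1, and Quality assurance provides for review of ungradable cases, so that charge is not supported.

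**Conclusion.** The point holds in a limited form. As defined, sensitivity and specificity apply to patients with gradable images, which is narrower than the real-world claim. The 1230 delivers an expected 246 DR cases only if every patient is gradable.

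The shortfall in precision is modest, affects sensitivity alone, and depends on an ungradable rate that the article does not state: ±5.1 to ±5.6 points at assumed rates of 5 to 20%. The effect on the estimate can be larger. At an assumed 10%, with DR status known and ungradable counted as positive, a gradable-only specificity of 80% becomes 72% over all screened patients. That 8-point change exceeds the 5-point margin planned for. These figures assume equal ungradable rates in DR and non-DR, and 80% accuracy among gradable patients. The sponsor should correct this, but it does not undermine the design.

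**What to change.** **Table 1**
- Label the present sensitivity and specificity as accuracy in patients with gradable images.
- Add the patient-level ungradable proportion, overall and per camera.
- Beside them, report an all-screened analysis in which an ungradable result counts as a positive (refer) screen. Apply the same rule to images that the AI cannot grade but the readers can.
- For patients with no image-based reference, show bounds with DR status taken as all DR and then as all non-DR.
- Use the eye-clinic examination of those who attend only as a labelled sensitivity analysis. As the main reference for this group it would introduce a second standard, and Sample size itself expects that patients with early DR may not comply with referral.

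**Sample size section**
- State that ±5 points for sensitivity assumes all images are gradable, and give the margin at the ungradable rate observed so far. Study timeline reports recruitment under way and an interim analysis one year after its start, so that rate should be obtainable.

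**Cost.** A few lines of wording and one further table, largely from data already collected. The sponsor accepts a less favourable specificity, a slightly wider stated margin for sensitivity, and bounds instead of a single figure for some patients. No clinical rule changes.

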**Methods and analysis:**

We will conduct a prospective cohort study comparing (i) the intervention cohort, screened at diabetes clinics and referred to eye clinics per the proposed pathway, and (ii) the standard-of-care (SOC) eye clinic cohort. The study will be conducted in Hyderabad, India, at LV Prasad Eye Institute and four IDEA (Institute of Diabetes, Endocrinology, and Adiposity) Clinics. The primary objective is to evaluate the effectiveness of a systematic diabetic retinopathy screening program in achieving earlier detection and reducing visual impairment among People With Diabetes (PWD) attending IDEA clinics compared to routine care at eye care settings. The screening program will be operationalized using AI-enabled tools and supported by trained non-medical technicians. We will perform visual acuity tests and non-mydriatic fundus photography using AI-assisted cameras. DR-positive patients will be referred for treatment and follow-up. We aim to achieve high accuracy (>90%) in appropriate referral of DR and high screening coverage (>80%) of eligible PWD. Success metrics include screening uptake, AI diagnostic accuracy, referral rates, cost-effectiveness, patient satisfaction, follow-up adherence, and long-term outcomes.

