### Objectives

The study aims to show that systematic screening leads to earlier detection of diabetic retinopathy (DR) and reduces visual impairment. It will compare the effectiveness of screening at physician clinics versus routine DR care in eye care settings. The screening program, supported by trained non-medical technicians, is AI-enabled and targets over 90% accuracy in appropriate referral of DR and 80% coverage of eligible people with diabetes (PWD).

The secondary objectives of the study are to: 1. Assess the cost-effectiveness of the AI-enabled systematic screening program and referral pathway compared to the current pathway at an eye care clinic. 2. Evaluate patient satisfaction and adherence to follow-up recommendations in the AI-enabled screening program versus the routine care pathway through an effective digital tracking system.

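### Table 1 prints patients referred as both numerator and denominator of the referral rate, so it is always 100%; the >90% referral-accuracy target also has no matching indicator

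*Protocol article*

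**What the plan says.** **Referral rate.** Table 1 (Program outcomes) gives each indicator a definition, a numerator and a denominator. For the referral rate these are:

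- definition: "Proportion of screened patients referred for further examination or treatment"
- numerator: "Number of patients referred for further examination or treatment"
- denominator: "Total number of patients referred"

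The Abstract lists referral rates among the success metrics. The Statistical analysis section names them among the key outcomes for the adjusted regression models.

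**Accuracy target.** The Abstract states: "We aim to achieve high accuracy (>90%) in appropriate referral of DR and high screening coverage (>80%) of eligible PWD". The Objectives repeat both targets. Coverage has a matching Table 1 row (screening uptake). Referral accuracy has none; the nearest rows are AI sensitivity, AI specificity and the ROC curve, all for DR against manual grading.

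**Sizing of the accuracy analysis.** The Sample size section works from "diagnostic accuracy with sensitivity and specificity set at 80" per cent, "assuming a 95% confidence level and a margin of error of ±5" per cent. It requires 246 DR-positive and 246 DR-negative cases, and 1230 patients screened.

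**Who decides on referral.** Under Study procedures, a technician reviews the images that the AI flags for DR, and the reading centre grades all images. A patient is referred for DR, for acuity below 20/60, for other retinal pathology or for ungradable images.

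**The concern.** The article fixes the referral-rate formula in print, and the formula cannot vary. An outcome that equals 100% by construction cannot be compared between groups, tracked over time or used as a regression outcome, and all readers have is a row whose cells disagree.

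The accuracy target raises a different question. The article sets a numerical goal and prints an indicator table that does not contain it. The referral-rate row cannot stand in: even when corrected, it measures how many patients are referred, not whether they should have been. The timely referral rates under Process evaluation measure promptness, not correctness. If the measure is chosen after results are seen, the same data could be reported as meeting or missing the target.

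**Working it through.** **1. Referral rate.** Let R be patients referred and N patients screened.

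- As printed: R / R = 100% for any R above 0.
- As defined in the same row: R / N.

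The article gives no expected referral count, so R below is illustrative; N = 375 is the number to be screened at the diabetes clinics.

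| R | Printed formula | Row's own definition |
|---|---|---|
| 75 | 100% | 75/375 = 20% |
| 120 | 100% | 120/375 = 32% |
| 300 | 100% | 300/375 = 80% |

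**2. The plan's accuracy sizing.** The single-proportion precision formula is n = 1.96² × p(1 − p) / d², with p = 0.80 and d = 0.05.

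- n = 1.96² × 0.16 / 0.0025 = 245.9, rounded up to 246. This matches the plan.
- 246 / 0.20 = 1230. This also matches.
- With p = 0.90 and the same d: n = 138.3, rounded up to 139, and 139 / 0.20 = 695 screened.

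The 80% planning value therefore gives a larger sample than 90% would. At a true value of 90%, the planned 246 DR-positive cases give a 95% half-width of about ±3.7 points. The 984 DR-negative patients expected among 1230 (1230 − 246) give about ±1.9 points.

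**3. What 80%/80% implies for DR.** The prevalence comes from the Sample size section: "Given the estimated 20% prevalence of diabetic retinopathy (DR) in the screened population".

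AI alone, as fractions of those screened:

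- true positives: 0.20 × 0.80 = 0.16
- false positives: 0.80 × 0.20 = 0.16
- true negatives: 0.80 × 0.80 = 0.64
- overall accuracy: 0.16 + 0.64 = 0.80

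The technician reviews AI positives only. Suppose a fraction f of the false positives is ruled out and no true positive is lost (an assumption favourable to the programme). Then:

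- overall accuracy = 0.80 + 0.16f
- specificity = 0.80 + 0.20f
- sensitivity stays at 0.80, because AI negatives are not reviewed at this stage; any true positive ruled out would lower it.

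| Stage | f | Overall accuracy | Sensitivity | Specificity |
|---|---|---|---|---|
| AI alone | 0 | 80% | 80% | 80% |
| AI plus technician | 0.625 | 90% | 80% | 92.5% |
| AI plus technician | 1 | 96% | 80% | 100% |

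On these planning values, a target above 90% is missed by AI alone. After technician review it can be met on overall accuracy or specificity but not on sensitivity. The reading centre's regrading could raise sensitivity further. However, a decision already corrected to the reading-centre grade and then judged against that grade would agree by construction, so the stage must be stated as well as the measure.

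**The case against.** **The denominator is a clerical slip.** The definition cell in the same row shows what was meant, so an analyst is unlikely to compute R / R. The referral rate is one of several programme indicators and plays no part in the comparison of disease stage that sizes the two arms. This stands, and it limits the severity. It does not make the row correct: the formula is stated, it is wrong, and the outcome is named elsewhere as a success metric and a modelled outcome.

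**The target is an aim without a decision rule, and a condensed article may leave its definition to the full protocol.** This has some force, which is why the point is secondary. Still, the article chose to print an indicator table, and the companion coverage target appears in it.

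A reader might go further in three ways that the document does not support.

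- *The >90% target conflicts with the 80% sizing value, or fails on the plan's own assumptions.* The 80% is a planning value for AI alone in a precision calculation that reproduces exactly. The target concerns referral by a programme that includes human review. The figures are unreconciled, not contradictory.
- *A poor tool could pass.* At 20% prevalence, sensitivity of 50% with specificity of 100% gives 0.10 + 0.80 = 90% overall accuracy. The article does not adopt overall accuracy as its measure, and Table 1 reports sensitivity in its own row, where 50% would be visible.
- *A reference for the full referral decision, including acuity, is already collected for everyone.* Beyond the 25-patient pilot and technician re-evaluation at refresher training, the quality assurance section describes comparison of acuity estimates only for referred patients. Sensitivity of the acuity component cannot be computed from what is described.

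**Conclusion.** The point holds on the referral rate: as printed it is always 100% and disagrees with its own definition. This rests on the table text alone and needs no assumption.

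The accuracy target lacks a matching indicator. On the plan's 20% prevalence and 80%/80% values, the candidate measures run from 80% (AI alone, or sensitivity after technician review) to at most 96% (overall accuracy after technician review) and 100% (specificity after technician review). The upper figures assume that every false positive and no true positive is ruled out. They cover DR only, not the other grounds for referral.

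Severity is minor to moderate. The comparison of disease stage between arms and the 246/1230 sizing are unaffected.

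**What to change.** 1. In the referral-rate row of Table 1, replace the denominator with the number of patients screened, as the row's definition already implies.
2. State which quantity the >90% target applies to, and at which stage. Preferably add one row giving sensitivity and specificity separately for the image-based referral decision after technician review, against the reading-centre grading, each with a 95% CI. Leave acuity-triggered referral out of this measure unless a reference acuity is obtained in non-referred patients.
3. Add one sentence saying that the 80% in the Sample size section is a planning value for AI alone, not the programme target. The sample size need not change.

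The cost is a table correction, one row and one sentence, with ethics committee clearance if handled as an amendment. No extra patients or examinations are needed: the reading centre already grades all images, and the quality assurance section already plans to compare AI, technician and reading-centre grades. Because recruitment is under way and an interim analysis is scheduled, the definition should be settled before accuracy results are examined.
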